### Procedure for unblinding if needed

N/A, the patient is not blinded to the allocated group.

## Data collection and management

### Plans for the assessment and collection of outcomes

In addition to what is obtained through the initial questionnaire, all information on baseline characteristics will be collected from Danish nationwide registries. This will be supplemented with data from the initial questionnaire on body mass index, smoking status (including pack-years), FEV1, and asthma. Information on adherence and symptom scores for exploratory outcomes will be obtained through questionnaires. The data from nationwide registries include age, gender, exacerbation history, comorbidities, and relevant medication details. All data used to assess clinical endpoints during the study will be collected from Danish nationwide registries.

### Plans to promote participant retention and complete follow-up

The trial will aim to ensure adherence and compliance with the allocated randomized group through electronic reminders (Table 4).

### Data management

All data will be saved on REDCap. A statistician will be responsible for the validity of analyses.

### Confidentiality

Personal information about potential and enrolled participants will be collected, shared, and maintained according to patient–physician confidentiality and GDPR.

### Plans for collection, laboratory evaluation, and storage of biological specimens for genetic or molecular analysis in this trial/future use

N/A

No biological specimens will be obtained in this trial.

## Statistical methods

### Statistical methods for primary and secondary outcomes

The primary and all secondary outcomes will be analyzed using the intention-to-treat (ITT) approach, which encompasses the entire cohort of randomized participants in the study. Additionally, per-protocol analyses will be conducted for patients taking inhalation medication 6–7 days per week at the allocated administration time for the full duration of the study, along with modified ITT (mITT) analyses for those who have taken less than 6 days or more than 2 days per week for any amount of time. These analyses will be performed on both the primary and all secondary outcomes, providing a comprehensive evaluation of the study’s results.

The primary outcome (hospitalization-requiring AECOPD or death from all causes within 12) will be presented as a fraction with percentage and relative risk with a 95% confidence interval. The groups will be compared using a two-sided binomial test. The same principles will be applied to secondary binomial outcomes. For the SABA pick-up rate, the incidence rate and ratios will be calculated and presented (including 95% confidence intervals) and compared using the chi-squared test. Changes in CAT and MRC (respectively) will be reported as median differences with IQR and compared within and between groups with a paired two-sided Wilcoxon signed-rank test and an unpaired two-sided Wilcoxon rank-sum test. A subgroup analysis will be performed on the primary outcome with the following subgroups: adherence group (high adherence: ≥4–5 days per week of adherence), age (≥65 years), asthma overlap, coexisting heart failure, body mass index (>30 kg/), frequent exacerbator (>1 severe exacerbation within 12 months prior to baseline), and treatment with systemic beta-2 antagonist at baseline. A *p*-value of <0.05 will be considered significant.

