**Methods:**

Randomized controlled open-label trial. Persons aged 30 years or older with a once-daily LAMA prescription and a confirmed COPD diagnosis were recruited. Participants were randomized in a 1:1 ratio to either morning or evening LAMA administration. Complete follow-up for the primary outcome, hospitalization-requiring AECOPD, or death from all causes within 1 year was captured from the Danish National Health Register, as were patient-reported outcome assessments at 6 and 12 months.

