### Outcomes

The primary efficacy endpoint is the occurrence of hospitalization requiring AECOPD or death from all causes within 12 months. Secondary efficacy endpoints included (i) moderate COPD exacerbations; (ii) all-cause hospitalization; (iii) ICU admission; (iv) need for non-invasive ventilation; (v) all-cause mortality; (vi) SABA use/pick-up rate; and exploratory endpoints (i) relation between adherence and AECOPD hospitalization, (ii) change in CAT score, (iii) change in MRC score, and (iv) change in “soundly sleeping” parameter of CAT.

The details on the primary and secondary outcomes of the study can be seen in Tables 1, 2, and exploratory outcomes in Table 3.

**Table 2 tab2:** Secondary and exploratory endpoint definition.

Endpoint	ICD-10/ATC codes	Inpatient/outpatient/minimum required length of stay/other criteria
Moderate COPD exacerbations	Prednisolone: H02AB06 or Antibiotics: J01CA04, J01AA02, J01CR02, J01MA14	Excluding hospitalizations and emergency room visits: DJ441 (A)
Hospitalization (all-cause)		Inpatient, length of stay ≥24 h
Hospitalization in ICU (all-cause)		Inpatient, ICU, length of stay ≥24 h
Need for NIV	BGDA1	A or B
Mortality (all-cause)		Participant registered as dead in the CPR register.
SABA use/pick-up rate	R03AC02, R03CC02, R03AC03	Danish National Prescription Registry
Change in CAT score	Questionnaire	At 6 and 12 months
Change in MRC score	Questionnaire	At 6 and 12 months

The time frame is ≥1 day after randomization until the end of the study (12 months from randomization) for all outcomes. A = primary discharge diagnosis and B = secondary discharge diagnosis. COPD, chronic obstructive pulmonary disease; ICU, intensive care unit; NIV, non-invasive ventilation; CPR, Central (National) Person Registry; SABA, short-acting beta-2 agonists; CAT, COPD assessment test.

**Table 3 tab3:** Exploratory endpoint definition.

Endpoint	Data source or ICD-10 codes	Inpatient/outpatient/minimum required length of stay/other criteria
Relation between adherence and hospitalization-requiring AECOPD	Questionnaire, DJ440, DJ441	For hospitalizations: Type A diagnosis (primary discharge diagnosis). Inpatient and length of stay ≥24 h, or emergency room visits. Deaths excluded.
Change in CAT score	Questionnaire	At 6 and 12 months
Change in MRC score	Questionnaire	At 6 and 12 months
Change in CAT “soundly sleeping” parameter	Questionnaire	At 6 and 12 months

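### As worded, the per-protocol set cannot contain participants who die, yet it is used for the composite with death and for mortality; adherence is also listed as a subgroup

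*Protocol article*

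**What the plan says.** All references are to the protocol article.

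- **Per-protocol set** (Statistical methods for primary and secondary outcomes): "patients taking inhalation medication 6–7 days per week at the allocated administration time for the full duration of the study". On the use of the per-protocol and modified intention-to-treat sets the section says: "These analyses will be performed on both the primary and all secondary outcomes".
- **Outcomes concerned** (Outcomes): "The primary efficacy endpoint is the occurrence of hospitalization requiring AECOPD or death from all causes within 12 months". All-cause mortality is also a secondary endpoint, defined in Table 2 as "Participant registered as dead in the CPR register". The time frame runs to 12 months from randomization.
- **Source of adherence data** (Plans for the assessment and collection of outcomes): "Information on adherence and symptom scores for exploratory outcomes will be obtained through questionnaires". Table 4 places questionnaires at day 1, month 6 and month 12.
- **Subgroups for the primary outcome** (same statistical section): the list opens with "adherence group (high adherence: ≥4–5 days per week of adherence" and continues with age, asthma overlap, heart failure, body mass index, exacerbation history and beta-antagonist treatment at baseline.
- **Exploratory adherence endpoint** (Table 3): "Inpatient and length of stay ≥24 h, or emergency room visits. Deaths excluded".

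The main analysis of the primary and all secondary outcomes is by intention to treat in the whole randomized cohort.

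**The concern.** An analysis set should not be defined by a condition that the outcome itself prevents people from meeting. Here membership requires adherent dosing through month 12, and one of the outcomes compared in the set is death before month 12. Taken at its word, the rule removes one component of the primary composite and the whole of a secondary endpoint.

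At stake is how the supportive result will be read. In an open-label trial that expects imperfect adherence, the per-protocol estimate is likely to be taken as the effect of actually dosing in the evening. If it covers survivors only, it answers a different question from the intention-to-treat composite beside it, and the two may diverge because deaths were dropped.

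The subgroup entry is a separate, smaller fault. Adherence to an allocated time exists only after allocation, and one arm is told to dose in the morning as usual while the other is assigned the evening. High adherers in the two arms need not be comparable, so the contrast within that group lacks the protection of randomization that the baseline subgroups have.

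**Working it through.** **1. Can a participant who dies meet the rule?** The rule needs adherence over the full study, and the study period is 12 months from randomization. Adherence is taken from questionnaires, the last at month 12. Someone who dies earlier has neither 12 months of dosing nor a month-12 answer. No section limits the requirement to the time until death or first event. As written, the answer is no.

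**2. The plan's own figures** (Sample size). The inputs are 20,000 admissions a year, of which 50% count, 6,000 deaths and 178,000 LAMA users.

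- Events: 0.5 × 20,000 + 6,000 = 16,000.
- Risk: 16,000/178,000 = 8.99% (printed as 8.9%).
- Sample size: with p1 = 0.08989 and p2 = 0.08989 × (1 − 0.25 × 0.844) = 0.07092, two-sided alpha 0.05, power 0.80 and a continuity correction, the result is 3,331 per arm, 6,662 in total. This matches the plan exactly.

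**3. What the rule removes, on those counts.**

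- Share of primary events that are deaths: 6,000/16,000 = 37.5%.
- Twelve-month death risk: 6,000/178,000 = 3.37%.
- Among 10,013 randomized: 10,013 × 0.0337 ≈ 338 deaths, within 10,013 × 0.0899 ≈ 900 primary events.
- Control composite risk among survivors: (16,000 − 6,000)/(178,000 − 6,000) = 10,000/172,000 = 5.8%, against 9.0% in all randomized.
- Mortality among survivors: 0 in each arm, so the relative risk is undefined.

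**4. Does this shift the composite relative risk?** Let d = 6,000/178,000 = 0.0337 and h = 10,000/178,000 = 0.0562, and let r_d and r_h be assumed relative risks for death and for hospitalization.

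- All randomized: RR = (d·r_d + h·r_h)/(d + h).
- Survivors only: RR = r_h·(1 − d)/(1 − d·r_d).

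| Assumed r_d | Assumed r_h | All randomized | Survivors |
|---|---|---|---|
| 1.00 | 1.00 | 1.00 | 1.00 |
| 0.75 | 0.75 | 0.75 | 0.74 |
| 0.75 | 1.00 | 0.91 | 0.99 |
| 1.25 | 0.75 | 0.94 | 0.76 |

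With no effect on either component, or the same effect on both, dropping deaths changes little or nothing. The estimate moves when the two effects differ. In the last row, excess deaths disappear from view and the apparent benefit grows.

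**5. Comparing adherers across arms** is a different mechanism, relevant to the subgroup. Suppose timing has no effect, evening adherence is 84.4% (the plan's figure), morning adherence is 95% (assumed), and non-adherers carry f times the risk (assumed). Then RR among adherers = (0.95 + 0.05f)/(0.844 + 0.156f).

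- f = 1.5: 1.025/1.078 = 0.95.
- f = 2.0: 1.05/1.156 = 0.91.
- Equal adherence in both arms: 1.00.

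The plausible range under these assumptions is therefore 0.91 to 1.00.

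**The case against.** The strongest reply is that nothing decision-bearing is touched. The intention-to-treat analysis covers everyone randomized, primary outcome data come complete from registries, the interim analysis is by intention to treat, and the section on protocol non-adherence calls the per-protocol analyses secondary. That stands, and it limits the severity. A reader might infer that the trial's main conclusion or its sample size is compromised; the document does not support that.

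A second reply is that full duration could mean until death or event, and that such operational rules belong in an analysis plan that is not shown. The exclusion would indeed not follow on that reading. But the article itself states the set, the duration and the outcomes, and the stated words do not say it. Adding the clause is the correction. Table 3's exclusion of deaths lends little support either way: it concerns a separate exploratory endpoint and may only mean that this endpoint is hospitalization and not the composite.

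Several stronger readings are tempting and should be resisted:

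- **That about 338 deaths are lost from the set.** This assumes that planning rates hold in self-enrolled participants and that everyone who died would otherwise have qualified. At 84.4% adherence the figure is about 338 × 0.844 = 285.
- **That removing deaths creates a spurious benefit when timing does nothing.** The first row of the table shows a relative risk of 1.00. The 0.91 to 0.95 figures come from assumed differences in adherence, not from removing deaths.
- **That a null effect could conceal harm.** If timing has no effect, there is no harm to conceal.
- **That every admitted participant is removed.** The questionnaire's wording and recall period are not given, so this is conjecture.

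**Conclusion.** The point holds as a moderate defect in the supportive analyses. The stated per-protocol rule, followed literally, turns the primary composite into AECOPD hospitalization among survivors and leaves all-cause mortality with nothing to estimate. If the planning counts apply to the trial and death is the only ground for exclusion, the set loses the 37.5% of primary events that are deaths, and the control risk drops from about 9.0% to about 5.8%. Non-response to questionnaires would shrink the set further by an amount the document does not allow one to state. The direction and size of any distortion in the relative risk cannot be known in advance; the worked values are illustrations under assumed effects.

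The adherence subgroup is a post-randomization grouping placed with baseline factors, and its result cannot be read as a randomized subgroup effect.

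**What to change.** Make these changes before the per-protocol analyses are run.

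- **Per-protocol set, option A.** Judge adherence only up to the first event, death or last contact, so that deaths are counted. State how someone with no follow-up questionnaire before death is classified. People with early events have had less time to fail the rule, so this comparison is still not randomized.
- **Per-protocol set, option B.** Use a month-6 landmark: classify adherence from the month-6 questionnaire among those alive then, count all later events including deaths up to month 12, and adjust for registry baseline covariates. Events in months 0 to 6 are lost, and the comparison remains observational.
- **Subgroups.** Remove adherence from the subgroup list, or report it only as an exploratory association labelled as non-randomized.
- **Optional.** A complier-average estimate keeps all randomized participants, but it needs a stated rule for adherence status in those who died or did not respond.

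The cost is protocol or analysis-plan wording and modest programming. No new data are needed.

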### Sample size

In Denmark, approximately 400,000 people are assumed to have COPD; however, approximately a quarter of them have not been diagnosed yet. We have data showing that 178,000 citizens have collected LAMA medication within the last 6 months. At the same time, we know that every year, there are approximately 20,000 admissions with AECOPD (severe AECOPD) and 6,000 deaths in patients with COPD. Assuming 50% of the AECOPD admissions are either unique or preceding a death, there are 16,000 annual events corresponding to our primary outcome. Thus, the annual risk of a primary outcome is approx. 16,000/178,000 = 8.9%. We hypothesize that evening LAMA administration will reduce the relative risk of the primary outcome by 25%, corresponding to a 2.2% absolute risk reduction. Assuming 84.4% uniformly distributed adherence to the intervention (= approximately 1 in 6 does not adhere), this corresponds to a relative risk reduction of 21.3% = 1.9% absolute risk reduction (average effect among all) in the ITT population. Alpha and power (1-beta) are set at 0.05 (two-sided) and 0.8, respectively. This leads to a needed sample size of 6,662 (3,331 + 3,331).

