### Methods in analysis to handle protocol non-adherence and any statistical methods to handle missing data

Secondary analyses will include mITT and per-protocol analyses to provide a comprehensive evaluation of the study outcomes. No data on the primary outcome will be missing as national registries will be used for outcome assessment. Only self-reported outcomes such as MRC and CAT can be expected to be missing. It will be assumed all missing data will be missing at random or completely at random to allow for multiple imputations. No imputed data will be presented in the baseline table.

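### The mITT set is defined by a condition that every adherence value meets; read with *and* instead, it shares no one with the per-protocol set

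*Protocol article*

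**What the plan says.** The section Statistical methods for primary and secondary outcomes names three analysis sets.

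- **ITT**, "which encompasses the entire cohort of randomized participants in the study".
- **Per-protocol**, for "patients taking inhalation medication 6–7 days per week at the allocated administration time for the full duration of the study".
- **mITT** (modified ITT), "for those who have taken less than 6 days or more than 2 days per week for any amount of time".

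On the two additional sets it says: "These analyses will be performed on both the primary and all secondary outcomes". The same section also sets a subgroup cut-off for adherence: "adherence group (high adherence: ≥4–5 days per week of adherence".

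The section on non-adherence and missing data names the mITT again without defining it: "Secondary analyses will include mITT and per-protocol analyses to provide a comprehensive evaluation of the study outcomes". According to the section on assessment and collection of outcomes, adherence is obtained by questionnaire. Table 4 places questionnaires at day 1, 6 months and 12 months.

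**The concern.** A modified ITT set usually consists of the randomized participants with a limited, stated exclusion, and it contains the per-protocol participants. The printed rule joins an upper bound (below 6) and a lower bound (above 2) with *or*. Two such overlapping bounds cover every possible value, so the rule does not select. Changing *or* to *and* gives a band that leaves out the most adherent participants. The closing words, which accept any length of time, loosen either reading, because one qualifying period is enough.

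The mITT is one of two named analyses addressing non-adherence, and it covers every primary and secondary outcome. Under the printed wording, agreement between mITT and ITT would tell a reader almost nothing, since the two sets are nearly the same people. Under the *and* wording, the mITT result would describe intermittent or partial adherers only. With the wording open, the choice between two very different sets could be made after adherence and outcome data are seen, in an open-label trial.

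**Working it through.** **Inputs.** The mITT, per-protocol and ITT rules and the high-adherence cut-off come from Statistical methods for primary and secondary outcomes. The two follow-up questionnaires come from Table 4. The design figures come from Sample size.

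**Step 1: single adherence value.** Let d be days per week, from 0 to 7.

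| d | d < 6 or d > 2 | d < 6 and d > 2 | Per-protocol range (6–7) |
|---|---|---|---|
| 0, 1, 2 | true | false | no |
| 3, 4, 5 | true | true | no |
| 6, 7 | true | false | yes |

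The *or* condition holds for 8 of 8 values. The *and* condition holds for 3 of 8.

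**Step 2: allowing for any amount of time.** Take two follow-up periods, each with 8 possible values: 8 × 8 = 64 patterns.

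- *Or*, at least one qualifying period: 64 of 64 patterns.
- *And*, at least one period at 3–5 days: five values (0, 1, 2, 6, 7) fail in a period, so 5 × 5 = 25 patterns fail and 64 − 25 = 39 qualify.
- Per-protocol, 6–7 days in both periods: 2 × 2 = 4 patterns. All 4 are among the 25 that fail the *and* rule, so the overlap is 0.
- The other failing patterns are 3 × 3 = 9 with 0–2 days throughout, and 2 × (3 × 2) = 12 that mix 0–2 with 6–7 days. The check is 4 + 9 + 12 = 25.

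These are counts of logical patterns. They are not estimates of how many participants fall in each.

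**Step 3: nesting.** Under *or*, mITT equals ITT among those with known adherence. Under *and*, mITT and per-protocol are disjoint. Neither gives a set lying strictly between per-protocol and ITT. A single lower bound (d > 2) applied over the same period as the per-protocol rule would contain it.

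**Step 4: does the design depend on the mITT set?** The stated sample size can be reproduced without it.

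- p1 = 16,000/178,000 = 0.08989.
- Diluted relative reduction = 0.25 × 0.844 = 0.211 (the plan prints 21.3%; the product is what reproduces its total).
- p2 = 0.08989 × (1 − 0.211) = 0.07092.
- Two-proportion formula, pooled variance, two-sided alpha 0.05, power 0.80, 1:1: 3,226 per arm. With continuity correction: 3,331 per arm, or 6,662 in total, which is the plan's figure.

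The dilution is applied to the ITT population, and the interim analysis is also specified on the ITT population. Neither uses the mITT rule.

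**The case against.** The strongest reply is that little depends on this sentence. The primary and all secondary outcomes are analysed by ITT, the interim analysis and sample size rest on ITT, and the mITT is called a secondary analysis. That stands, and it sets the severity.

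A second reply is that nesting is a convention the protocol never states. With *and*, the text could describe adherence bands: full adherence as per-protocol and partial adherence as the other group. That is coherent, but then the label mITT is wrong and the printed *or* still has to be changed.

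A third reply is that an analysis plan may settle the definition. It may, but the article does not leave the set undefined. It prints a rule that selects no one out, and a plan that copied the rule would carry the same fault.

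Three stronger inferences are tempting, and the documents do not support them.

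- **That the *and* reading leaves poor adherers only.** It selects 3–5 days, drops those who stay at 0–2 days, and admits someone at 6–7 days for most of the year with one period at 3–5. The same section's subgroup counts 4–5 days and above as high adherence.
- **That the number dropped under *and* can be read from the sample-size section.** The phrase "Assuming 84.4% uniformly distributed adherence to the intervention" is not tied to any days-per-week threshold. It serves only to dilute the effect, so it cannot be turned into a count of participants at 6–7 days.
- **That the mITT equals all 10,013 randomized participants.** Adherence is self-reported, so those who do not respond, or who die before 6 months, may be impossible to classify, and the article does not say how they are handled.

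**Conclusion.** The point holds as a should-fix. As printed, the mITT condition is a tautology: 8 of 8 values and 64 of 64 two-period patterns meet it. The mITT analyses therefore essentially duplicate the ITT for everyone with known adherence. With *and*, the set is participants with a period at 3–5 days per week, has zero overlap with per-protocol, and is not a modified ITT set as usually understood. No other section resolves which was meant.

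A reader might infer that the trial's main conclusion is at risk. It is not, because the primary ITT comparison, the interim analysis and the sample size of 6,662 are untouched. What fails is one named secondary analysis, planned for the primary and all secondary outcomes.

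The tautology follows from the wording alone. The remark about nesting rests on the usual meaning of modified ITT. How many participants would move between readings cannot be computed from the article.

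**What to change.** Before outcome data are analysed by arm, choose one of the following.

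1. **Replace the sentence with a single rule** that uses the protocol's own lower bound. For example: the mITT set is all randomized participants who report using their LAMA at the allocated time on more than 2 days per week, including those at 6–7 days, so that per-protocol lies within mITT and mITT within ITT. State the period over which the rule must hold and how participants without adherence data are handled. The trial team must confirm that this lower bound is what was intended.
2. **If a 3–5 day group was intended**, write *and*, state the duration rule, and call it a partial-adherence analysis instead of mITT.
3. **Delete the mITT analysis** and keep ITT and per-protocol.

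Under options 1 and 2, present the result as supplementary to the ITT, because the set is selected on self-reported adherence after randomization and the comparison is no longer protected by it.

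The cost is one or two sentences in the protocol and any analysis plan. No new data are needed, and the primary analysis and sample size do not change.

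### The primary test is named loosely as an unadjusted binomial test; one two-sample method, adjusted for registry baseline variables, should supply both the p-value and the relative risk interval

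*Protocol article*

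**What the plan says.** Under Statistical methods for primary and secondary outcomes, the protocol article says that the primary outcome "will be presented as a fraction with percentage and relative risk with a 95% confidence interval". It then names the test: "The groups will be compared using a two-sided binomial test". The next sentence extends this to the binary secondary outcomes. No covariates and no adjusted analysis are named. Age, asthma overlap, heart failure, body mass index and frequent exacerbation appear there only as subgroups.

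Under Plans for the assessment and collection of outcomes, the article lists what is already held: "The data from nationwide registries include age, gender, exacerbation history, comorbidities, and relevant medication details".

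Under Sample size, "Alpha and power (1-beta) are set at 0.05 (two-sided) and 0.8, respectively". The trial is sized as a comparison of two risks, with 3,331 per arm (6,662 in total). The Abstract reports 10,013 randomized.

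**The concern.** A binomial test, in ordinary usage, compares one observed proportion with a fixed value. It is not the name of a two-group test, and it does not produce a relative risk or its interval. The same section gives proper two-group names for other outcomes (a chi-squared test for short-acting beta-agonist pick-up, a rank-sum test for symptom scores), so the primary outcome has the least exact label. In an open-label trial the primary test should not be left to interpretation once data are available.

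The second part is efficiency. The comparison is described without covariates, although registry variables that plausibly predict admission or death are on file for the trial. The Discussion says that survivors of an admission for exacerbation are at higher risk of another, so exacerbation history at least is thought to be prognostic. At stake are a clear primary p-value that belongs to the reported estimate, and some precision that needs no further data collection.

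**Working it through.** **1. Reproduce the planned size, to see which test was meant.** Inputs from Sample size: control risk p1 = 16,000/178,000 = 0.08989 (printed as 8.9%); relative reduction 25%; adherence 84.4%; two-sided alpha 0.05; power 0.80.

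- Diluted reduction: 0.25 × 0.844 = 0.211 (the article prints 21.3%; its sample size matches 21.1%).
- p2 = 0.08989 × (1 − 0.211) = 0.07092; difference d = 0.01897; mean risk 0.08040.
- Two-proportion formula with pooled variance under the null: n = [1.96·√(2·0.08040·0.91960) + 0.8416·√(p1(1−p1) + p2(1−p2))]² / d² = (0.7537 + 0.3234)² / 0.01897² ≈ 3,226 per arm.
- Continuity correction: n/4 · [1 + √(1 + 4/(n·d))]² = 3,330.1, rounded up to **3,331 per arm, 6,662 in total**.

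The published number is reproduced exactly by a two-sample comparison of proportions.

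**2. What each reading of the test name would do.** Simulated with 200,000 replicates, control risk 8.9%, relative reduction 21.3%:

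| Reading | Type I error | Power, 3,331 per arm | Power, 5,006 per arm |
|---|---|---|---|
| Usual two-sample test | 4.9–5.0% | 81.7% | 93.9% |
| Split of all events against 50:50 | 3.9–4.0% | 79.4% | 92.9% |
| Observed morning risk treated as a fixed null | 16.6% | – | – |

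The last figure also follows directly. Ignoring the sampling error of one arm halves the variance of the difference, so the true error is 2·[1 − Φ(1.96/√2)] = 0.166. On the two-sample reading, the test and the Wald interval for the relative risk disagree in fewer than 0.1% of simulated trials.

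**3. What adjustment would add.** The document gives no measure of prognostic strength, so the explained share of outcome variance, R², is an assumption. C-statistics of 0.64, 0.70 and 0.75 at an assumed 7% event risk give R² of about 1.7%, 4.0% and 7.3%. At the planned control risk, c-statistics of about 0.64 and 0.75 give 2.1% and 8.6%. Effective size is approximated as n/(1 − R²).

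| Assumed R² | Equivalent extra patients, of 10,013 | Power, 3,331 per arm | Power, 5,006 per arm |
|---|---|---|---|
| 0 (unadjusted) | – | 81.6% | 93.9% |
| 1.7% | 173 (1.7%) | 82.2% | 94.3% |
| 4.0% | 417 (4.2%) | 83.1% | 94.7% |
| 7.3% | 789 (7.9%) | 84.4% | 95.4% |

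For example, at R² = 7.3%: 1/(1 − 0.073) = 1.079, so 5,006 per arm acts like about 5,400. These powers come from the formula without continuity correction, for 8.9% against 7.0%.

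**The case against.** A reader might infer that the primary test will run at a type I error of 16% to 17%. The document does not support that. Its sentence says that the groups are compared with each other, a relative risk with an interval is reported, the interim analysis uses Z-scores for the primary endpoint, and the sample size is a two-proportion calculation. The following sentence applies the word binomial to outcomes, where it plainly means binary. A two-sample test on a binary outcome is therefore the natural reading, and it behaves properly. Even the event-split reading is only conservative. This objection stands: the defect is an inexact name, not a planned one-sample analysis.

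A reader might also infer that leaving out covariates is an error, or that the registry variables are known to be powerful predictors. Neither follows. Under 1:1 randomization with registry outcomes the crude intention-to-treat comparison is valid, and no section quantifies prognostic strength. With 10,013 randomized against 6,662 required, power on the plan's assumptions is already well above 80%, so the gain is modest. An analysis plan that is not shown may also specify an adjusted model. These points stand and limit the size of the concern. They do not remove the case for improvement: the article does fix a test for its main comparison, the name is not exact, and the variables for a more precise estimate are already collected.

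**Conclusion.** The concern holds in a limited form. The named test is strictly a one-sample test and is not linked to the relative risk interval, although a two-sample comparison is clearly intended and has a type I error of about 5%. The unadjusted analysis is valid but forgoes some precision. Under an assumed R² of about 2% to 7%, the loss equals roughly 2% to 8% of the patients, or about 0.4 to 1.5 points of power at the number randomized. These figures rest on the plan's control risk and effect and on an R² that the document does not give. This is an improvement in clarity and efficiency, not the correction of an invalid analysis.

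**What to change.** Replace the test name with one two-sample method that yields both the p-value and the relative risk with its 95% interval. Modified Poisson regression with robust variance, or logistic regression standardized to a marginal relative risk, would serve. Prespecify a short covariate set, for example age, sex, number of severe exacerbations in the previous 12 months and heart failure, all within the categories that the article says come from registries. Report the crude two-sample risk ratio as support, and use the same approach for the binary secondary outcomes. If the analysis plan already contains such a model, the protocol wording should be aligned with it.

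The cost is a few lines of text and minor programming. No new data are needed. The choice should be fixed before anyone sees outcomes by arm.
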